**Fig. 3 Fig3:**
[figure not shown]
Overall design of the Take a STAND for Health intervention

#### The constructs of Take a STAND for Health 

This intervention is founded on the constructs of self-determination theory. This theory argues that people have inherent growth tendencies and innate psychological needs (i.e., autonomy, competence, and relatedness), which are the basis for intrinsic motivation and behavior. A positive environment (i.e., one that satisfies all of these needs) could result in increased motivation and enduring behavioral changes. Take a STAND for Health effectively incorporates all of these needs: autonomy is stimulated because patients actively take part in goal setting; competence is accomplished since the goals are individualized and achievable; and relatedness is fostered by the monthly individual meetings, and the integrating environment that is fostered by the supportive phone calls and text messages. The Take a STAND for Health intervention was based on the Small Steps program [33], which was developed on the same principles, and was shown to be effective in reducing sedentary time (by 51 min/day) in older adults.

#### Goals domains and description

Goals will be separated into the following domains: (1) transport, which involves reducing sedentary time during transportation (e.g., park further away from your destination except when carrying a heavy weight, or alight from the bus a stop before or after your destination); (2) work, which involves reducing sedentary behavior at the workplace (e.g., stand up every 30 min while performing activities in a seated position or stand up during meetings and invite your colleagues to join you); and (3) leisure/social activities, which involve reducing time spent in sedentary behavior during leisure time (e.g., stand up during advert breaks when watching television or walk with your dog at least twice a week).

#### Sessions aims and structure

During session 1, a trained researcher will explain the details of the intervention (e.g., aim, duration, frequency, compliance) to the patient. Subsequently, they will be asked to talk about their daily routines and choose goals to reduce time spent in sedentary behavior, including goals from each domain, from a list of prespecified items. Goals will be explained in more detail if necessary and all possible questions will be clarified before patients set the goal. Patients will be encouraged to actively select their own goals; however, the researcher will assist them in opting for goals that could be feasible to incorporate into their daily routine. Patients will be advised to adhere to their goals throughout the intervention and will receive a summary of the goal-setting plan and will be requested to return individually tailored feedback (using a diary) in the next session.

During the following sessions, each patient will be asked about the execution of her goals and encouraged to report barriers and facilitators to achieving her goals. If a patient is adhering to the goals, she will be encouraged to maintain her routine. If not, the researcher will discuss ways of overcoming the reported barriers; if a barrier is considered to be unresolvable, the patient will be guided in selecting a new goal. The patient will deliver the diary and receive another one to be filled out and returned in the next session. Patients will be permanently encouraged to increase the reduction in sedentary time or increase the frequency of sit-to-stand transitions. In the last session, each patient will be asked about the feasibility of and adherence to the intervention, and barriers and facilitators for reducing sedentary behavior throughout the intervention.

#### Results and lessons from the pilot study

Seventeen young healthy participants (8 women and 9 men; age 26.4 ± 3.4 years; body mass index (BMI) 24.4 ± 3.0 kg/m^2^) were recruited to undertake a pilot study of the Take a STAND for Health intervention (as per the description above), with the exception being the total number of the goals, which were set up to 15 originally. Before the intervention, sedentary time was assessed during 7 days (baseline), and participants were instructed to follow their usual routine. Thereafter, participants undertook the Take a STAND for Health intervention during the following 14 days (Post). Sedentary behavior was monitored throughout the entire 21-day period using ActivPAL micro™ (PAL Technology, Glasgow, UK). Generalized linear mixed models were analyzed to test changes in sitting, standing, and stepping time, with time as a fixed factor, and patients as a random factor. Cohen’s *d* effect size (ES) was also calculated to determine change in sedentary time. The level of significance was set at *p* ≤ 0.050.

Participants spent most daily hours in sedentary behavior (10.0 ± 1.3 h/day), followed by standing and stepping (4.2 ± 0.9 and 1.8 ± 0.5 h/day, respectively). After the intervention, participants reduced their time spent in sedentary behavior by 0.6 h/day (*p* = 0.032; 95% confidence intervals (CI) 0.1, 1.2 h/day; ES = 0.55), increased time spent standing (mean difference 0.6 h/day; 95% CI 0.2, 1.0; *p* = 0.006), and maintained time spent stepping (mean difference 0.02 h/day; 95% CI − 0.2, 0.2; *p* = 0.821) (Fig. 4). After the intervention, participants reported that it was difficult to remember and follow all selected goals. According to several participants, the number of goals was excessive, and occasionally they did not fit their routines. Based on this feedback, we decided to reduce the number of goals and maintain only those with the best chance of being effectively incorporated into the patients’ routines.

**Fig. 4 Fig4:**
[figure not shown]
Time spent in sedentary behavior, standing, and stepping (hours/day) before and after the pilot study. *Significant difference when compared to baseline (*P* < 0.050)

### Study procedures

#### Sedentary behavior (primary outcome)

Postural allocation (sitting, standing, and stepping) will be measured using activPAL micro™ (PAL Technology, Glasgow, UK) activity-based accelerometers. Patients will wear the accelerometer for 7 days consecutive (24 h/day); the accelerometer will be fitted using tape (3 M, Tegaderm®, adhesive tape) onto the right medial front thigh, orientated with the x-axis pointing downward, y-axis horizontally to the left and z-axis horizontally forward. Data will be exported from the device using ActivPAL3™ software, v. 7.2.32 (PAL Technology, Glasgow, UK). ActivPAL™. Data will be reported as follows: time spent sitting and lying (hours/day), in prolonged sitting (hours/day), standing (hours/day), and stepping (hours/day), number of breaks in sedentary time, and mean daily waking time (calculated as: 24 h − time spent sleeping). All data will be standardized to a 16-h day to avoid bias from differences in patients’ wear time, using the formula: (data × 16)/wear time.

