#### Physical activity level

Physical activity levels will be objectively measured using the actiGraph GT3X® accelerometers (ActiGraph, Pensacola, FL, USA). All patients will be instructed to wear the accelerometer during waking hours for 7 days consecutive, except when bathing or swimming. The device will be worn on a belt at the waistline on the right side of the hip. Data will be exported in 60-s epochs using ActiLife 6 software, v. 6.11.9 (ActiGraph, Pensacola, FL, USA). Patients will have to accumulate at least 10 h of valid activity recordings per day for at least 4 days, including one weekend day. Non-wear periods will be defined as intervals of at least 60 min of zero activity counts, assuming as tolerance no more than 2 min of counts between 0 and 100. Freedson cut-points will be used to define epochs: sedentary time (< 100 counts per minute (cpm)), light-intensity physical activity (≥ 100 to < 1952 cpm), and moderate-to-vigorous physical activity (≥ 1952 cpm) [36]. Actigraph GT3X® data will be reported as follows: time spent in sedentary behavior (hours/day), light-intensity physical activity (hours/day), moderate-to-vigorous physical activity (minutes/day), and moderate-to-vigorous physical activity accrued in ≥ 10-min bouts (minutes/day), total counts, and mean daily wear time. All data will be standardized to a 16-h day to avoid bias from differences in patients’ wear time, using the formula: (data × 16)/wear time.

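### The activPAL primary outcome is scaled by 16/wear time although the device is worn 24 h/day; as printed, the rule counts sleep and cuts effects in hours, minutes or counts by one third

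*Protocol article*

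**What the plan says.** All of the rule is in the protocol article, Study procedures.

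- **Sedentary behavior (primary outcome).** On wear: "Patients will wear the accelerometer for 7 days consecutive (24 h/day". The first variable reported is "time spent sitting and lying (hours/day", followed by prolonged sitting, standing, stepping and breaks. The list ends with "mean daily waking time (calculated as: 24 h − time spent sleeping". Then: "All data will be standardized to a 16-h day to avoid bias from differences in patients’ wear time", "using the formula: (data × 16)/wear time". Wear time is not defined for this device, and nothing says that sleep is removed from sitting and lying.
- **Physical activity level.** The ActiGraph carries the identical scaling sentence, but there patients are "instructed to wear the accelerometer during waking hours for 7 days consecutive".
- **Results and lessons from the pilot study.** The same type of activPAL device gave 10.0 h/day sedentary, "followed by standing and stepping (4.2 ± 0.9 and 1.8 ± 0.5 h/day, respectively".

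**The concern.** For a device worn only while awake, wear time is close to waking time, and scaling to 16 h puts patients with different waking days on a common footing. For a device worn 24 h/day, wear time is about 24 h for everyone. The formula then no longer does what the article says it is for. It becomes a fixed multiplier, applied to a variable that includes time asleep unless sleep is taken out.

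This is the only primary outcome. At stake are what the outcome measures (waking sitting, or sitting plus sleep), the size of the effect in hours or minutes that readers will interpret, and its comparison with the figures the article itself uses: 10.3 h/day in the Introduction, 52 min under Sample size and 38 min/day from the pilot. The Statistical analysis section also splits patients into responders and non-responders by change in sedentary time. Any cut-off in minutes would mean something different under each reading.

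**Working it through.** **Inputs from the article:** target day 16 h; activPAL wear 24 h/day; 10.3 h/day sedentary in rheumatoid arthritis (Introduction); 52 min and effect size 0.58 (Sample size); 38 min/day (intervention section); pilot 10.0, 4.2 and 1.8 h/day. **Assumption, not in the article:** sleep of 6 to 9 h.

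**1. The pilot and the 16-h day.** 10.0 + 4.2 + 1.8 = 16.0 h, so the pilot figures fit a 16-h standardised day.

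**2. What each reading gives.** Take 10.3 h waking sedentary time and 8 h sleep, so waking time is 24 − 8 = 16 h.

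| Reading | Formula | Result |
|---|---|---|
| Waking data over waking time | 10.3 × 16/16 | 10.3 h |
| 24-h sitting and lying over 24 h (literal) | (10.3 + 8) × 16/24 | 12.2 h |
| Sleep removed, but still over 24 h | 10.3 × 16/24 | 6.9 h |

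For 7 and 9 h sleep the literal reading gives 17.3 × 16/24 = 11.5 h and 19.3 × 16/24 = 12.9 h.

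**3. Does the literal rule adjust for anything?** Hold upright time at 6 h. With full wear, sitting and lying is 24 − 6 = 18 h whatever the sleep, and 18 × 16/24 = 12.0 h at 6, 7, 8 and 9 h sleep. The waking rule, (24 − sleep − 6) × 16/(24 − sleep), gives 10.67, 10.35, 10.0 and 9.6 h. So the literal rule does not respond to waking time, and an hour moved from waking sitting to sleep registers as no change.

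**4. Effects in natural units.** With full wear the literal factor is 16/24 = 0.667: 52 min becomes 34.7 min and 38 min becomes 25.3 min. Break counts shrink in the same proportion. Under the waking rule the factor is 16/(24 − sleep): 0.889, 0.941, 1.000 and 1.067 for 6, 7, 8 and 9 h sleep, so 52 min becomes about 46 to 55 min.

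**5. Standardised effects.** A constant cancels in Cohen's d. If 0.58 is a mean difference over an SD, the SD is 52/0.58 = 89.7 min. Scaled by 2/3, the SD is 59.8 min, and 34.7/59.8 is again 0.58. Test statistics, p-values and power are likewise unaffected by the constant.

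**6. Scaling of waking time itself.** The sentence covers all data, and waking time is on the list. With a 24-h denominator, 16 h awake becomes 16 × 16/24 = 10.7 h. With a waking denominator, every patient's waking time becomes 16 h. Neither is a usable result.

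**The case against.** The strongest reply is that the literal reading is not the intended one. A 16-h target makes sense only for a waking day. The activPAL section goes to the trouble of deriving waking time, and it stands in the list where the ActiGraph section has mean wear time, as if it were the counterpart denominator. The pilot components add to 16.0 h. How sleep is detected is also detail that a condensed article may leave to the full protocol or the analysis plan.

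Most of this stands as evidence of intent. The missing sleep-detection method is not the complaint. The complaint is that the article states a rule for its primary outcome, names a denominator that it elsewhere puts at 24 h, and applies the rule to all data, which fails for waking time on either reading.

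Three stronger inferences are tempting, and the article does not support them.

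- **That the trial loses power or its effect size shrinks.** The constant changes neither. Counting sleep could change the variability of the outcome, but the article gives no sleep SD and no correlation between sleep and sitting. Over a full 24 h, sitting plus lying is simply 24 h minus upright time, so its SD need not be larger.
- **That the pilot sum proves which denominator was used.** Waking data over waking time and 24-h data over 24 h both sum to 16 h. The sum excludes only mixed forms: with 8 h sleep, waking data over 24 h would sum to 10.7 h, and 24-h data over waking time to 24 h. The 24-h reading would imply raw pilot values of 10.0 × 24/16 = 15.0 h sitting or lying and 6.0 × 24/16 = 9.0 h upright, hence less waking sitting than upright time for anyone sleeping more than 6 h. That favours the waking reading, but only with an assumption about sleep.
- **That the reported results will be one third too small.** This follows only if the formula is applied as printed.

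**Conclusion.** The point holds as a fault in a stated rule. With full 24-h wear, the printed formula counts sleep as sedentary time, multiplies everything by 16/24 without adjusting for waking time, and reports effects in hours, minutes or break counts one third below their unscaled size (52 min as 34.7 min). Cohen's d, p-values and power are not touched by the constant. The article's own clues point to a waking-day denominator, so this is a rule that misstates its probable intent, not a demonstrated error in the results.

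The 34.7 min rests on full 24-h wear; with gaps in wear the factor would differ from 0.667. The spread of 6.9, 10.3 and 12.2 h/day rests on the assumed 8 h sleep. How the cited 10.3 h and 52 min were processed cannot be seen from the article, so the loss of comparability with them is likely under the literal reading but not shown.

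**What to change.** Replace the activPAL scaling sentence with one to this effect: sitting/lying, prolonged sitting, standing, stepping and breaks are computed within waking wear time only, with sleep periods removed, and standardised as (data × 16)/waking wear time; waking time itself is reported unstandardised. Waking wear time can be defined as 24 h minus sleep minus non-wear. Keep the existing formula for the ActiGraph, where wear time already approximates waking time.

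The cost is one sentence. Sleep time is already to be derived for the waking-time variable, so no new data or assessments are needed. The wording should be settled before the activPAL data are analysed by group, so that the choice among readings is not made with the results in view.

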#### Physical activity level

Physical activity levels will be objectively measured using the actiGraph GT3X® accelerometers (ActiGraph, Pensacola, FL, USA). All patients will be instructed to wear the accelerometer during waking hours for 7 days consecutive, except when bathing or swimming. The device will be worn on a belt at the waistline on the right side of the hip. Data will be exported in 60-s epochs using ActiLife 6 software, v. 6.11.9 (ActiGraph, Pensacola, FL, USA). Patients will have to accumulate at least 10 h of valid activity recordings per day for at least 4 days, including one weekend day. Non-wear periods will be defined as intervals of at least 60 min of zero activity counts, assuming as tolerance no more than 2 min of counts between 0 and 100. Freedson cut-points will be used to define epochs: sedentary time (< 100 counts per minute (cpm)), light-intensity physical activity (≥ 100 to < 1952 cpm), and moderate-to-vigorous physical activity (≥ 1952 cpm) [36]. Actigraph GT3X® data will be reported as follows: time spent in sedentary behavior (hours/day), light-intensity physical activity (hours/day), moderate-to-vigorous physical activity (minutes/day), and moderate-to-vigorous physical activity accrued in ≥ 10-min bouts (minutes/day), total counts, and mean daily wear time. All data will be standardized to a 16-h day to avoid bias from differences in patients’ wear time, using the formula: (data × 16)/wear time.

#### Clinical assessment

Disease activity will be assessed by the Disease Activity Score in 28 joints [37], which is based on the number of tender and swollen joints, C-reactive protein or erythrocyte sedimentation rate, and the patient’s general health status. Higher scores represent more severe disease activity. The Health Assessment Questionnaire [38], which evaluates physical functioning in eight domains of daily life, will also be used; higher scores represent greater disability. Disease duration, current dose of prednisone, current use of biological agents (e.g., anti-TNF, anti-IL6, anti-IL1, B cell depleting-agents, and T cell activation-inhibiters), non-biological disease-modifying anti-rheumatic drugs (e.g., methotrexate, leflunomide, and hydroxychloroquine), and other medications will be obtained by reviewing medical records and interviewing patients. Pain will be assessed using a visual analogic scale [39], in which patients grade their pain using a 10-point scale; 0 means no pain and 10 means severe or unbearable pain. Fatigue will be assessed by the Fatigue Severity Scale [40] in which lower scores indicate lower fatigue.

#### Anthropometry and body composition

Height will be measured by a wall-mounted stadiometer. Body mass will be measured by a digital scale, with a sensitivity of 100 g. BMI will be calculated using the following equation: body mass (kg)/height (m)^2^. Waist circumference will be measured using a plastic tape measure placed around the smallest circumference between the lowest margin of the ribs and the upper margin of the iliac crest, with subjects standing. Body composition (i.e., bone, lean and fat mass, and visceral adipose tissue) will be measured by dual-energy x-ray absorptiometry (DXA), using a Lunar iDXA densitometer (GE Healthcare, WI, USA). All assessments will be performed by the same trained technician.

#### Aerobic conditioning

Patients will undergo a maximal graded exercise test on a treadmill (Centurion 200, Micromed, Brazil), with increments in velocity and grade at every minute until volitional exhaustion. Oxygen consumption (VO_2_) and carbon dioxide output will be obtained through breath-by-breath sampling and expressed as a 30-s average using an indirect calorimetric system (Cortex - model Metalyzer IIIB, Leipzig, Germany). Heart rate (HR) will be continuously recorded at rest, during exercise, and at recovery, using a 12-lead electrocardiogram (Ergo PC Elite, Inc. Micromed, Brazil). The test will be considered maximal when one of the following criteria is met: plateau in heart rate and VO_2_ with incremental workloads, respiratory exchange ratio > 1.1, and HR no less than 10 beats below age-predicted maximal HR. VO_2_ peak will be considered as the average of the final 30 s of the test [41]. Ventilatory thresholds will be identified following previously described procedures [42]. In brief, the ventilatory anaerobic threshold will be determined when ventilatory equivalent (VE) for VO_2_ (VE/VO_2_) increases without a concomitant increase in ventilatory equivalent for carbon dioxide (VE/VCO_2_). The respiratory compensation point will be determined when VE/VO_2_ and VE/VCO_2_ increase simultaneously.

#### Muscle function

Muscle function will be evaluated by the Timed-Stands, the Timed-Up-and-Go, and handgrip tests. A familiarization trial will be performed at least 48 h prior to the tests.

The Timed-Stands test evaluates the maximum number of stand-ups that a subject can perform from a standard armless chair within 30 s [43]. The Timed-Up-and-Go test evaluates the time required for the subject to rise from a standard armless chair, walk towards a line drawn on the floor 3 m away, turn, return, and sit back down again [44]. Patients will perform two maximal attempts of each test, with 2-min recovery periods between sets. Subsequently, patients will perform the handgrip test using a handgrip dynamometer (Takei A5001 Hand Grip Dynamometer, Takei Scientific Instruments Co., Ltd., Tokyo, Japan). The protocol consists of three maximal isometric contractions during 5 s interspersed with 60-s recovery periods. Patients will be instructed to squeeze the dynamometer as hard as possible. The maximum score achieved will be recorded in kilograms [45].

#### Blood pressure

Blood pressure will be measured by the auscultatory technique using a non-mercury sphygmomanometer [46]. All measurements will be taken in the same arm by a trained evaluator.

A random sub-sample of patients will undertake a 24-h ambulatory monitoring of arterial pressure (Dyna-MAPA, CARDIOS, Sao Paulo, Brazil). The monitoring device will be programmed to take readings every 15 min. Patients will record their activities in a diary during a 24-h period, including when they slept and woke up. Data will be analyzed using the Dyna-MAPA software (only data with at least 80% of the reading will be considered) and will be reported as 24-h, daytime and night-time, mean systolic and diastolic blood pressure; 24-h, daytime and night-time, systolic and diastolic blood pressure load (calculated as percentage of values above 130/80, 135/85, and 120/70 mmHg); morning surge in systolic and diastolic blood pressure (calculated as follows: mean systolic/diastolic blood pressure for 2 h after wake up – the lowest 2-h mean values of systolic/diastolic blood pressure during sleep); and nocturnal systolic and diastolic blood pressure fall (calculated as follows: [(mean day time systolic/diastolic blood pressure – mean night time systolic/diastolic blood pressure)/mean day time systolic/diastolic blood pressure] × 100).

#### Cardiovascular autonomic function

A random sub-sample of patients will undertake cardiovascular autonomic assessments, which will comprise continuous assessments of heart rate using a 3-lead electrocardiogram, beat-by-beat blood pressure via finger photoplethysmography (Finometer, Finapress Medical System, Arnhem, The Netherlands), and muscle sympathetic nerve activity via microneurography. These signals will be registered using a data acquisition system (Powerlab, AD Instruments, São Paulo, Brazil) and Labchart software (AD Instruments, São Paulo, Brazil), with a sampling rate of 1000 Hz per channel. Assessments will be performed at rest in a supine position. Patients will be instructed to remain quiet and to breathe spontaneously during the 30-min assessment.

Heart rate variability will be analyzed in 5-min segments during rest using the CardioSeries software (v 2.4, São Paulo, Brasil) [47]. Initially, the RR interval time series will be generated from the electrocardiographic signals. Afterwards, the time domain parameters - standard deviation of RR intervals and square root of the mean’ of the sum of the squares of differences between adjacent normal RR interval - will be calculated. For frequency domain analysis, the RR interval time series will be detrended (smooth prior), resampled at 4 Hz, and decomposed using the fast Fourier transform algorithm. The components of low (LF, 0.04–0.15 Hz) and high (HF, 0.15–0.4 Hz) frequencies will be calculated as described elsewhere [48].

The analysis of muscle sympathetic nerve activity will be performed using Labchart (v 2.4, São Paulo, Brasil) software. The sympathetic bursts will be automatically identified using the automatic peak detection function. Occasional misdetections will be manually corrected by an experienced evaluator. The muscle sympathetic nerve activity will be expressed as burst frequency (bursts/minute) and burst incidence (burst/100 heart beats).

Cardiac and sympathetic spontaneous baroreflex sensitivity will be assessed from the fluctuations of the RR interval, blood pressure, and muscle sympathetic nerve activity, using CardioSeries (v. 2.4, São Paulo, Brasil) software. Cardiac baroreflex sensitivity will be assessed using the sequence technique [49]. Sympathetic baroreflex sensitivity will be assessed from the linear regression analysis between the area of sympathetic bursts and the corresponding diastolic blood pressure. The slope of the linear regression line will be used as an index of sympathetic baroreflex sensitivity [50].

